## **Definitions**

### ***Confirmed iGAS infection:***

- Clinical presentation consistent with iGAS\* AND
- Isolation of group A streptococcus by culture or PCR or antigen detection test from a **normally sterile** body site

### ***Probable iGAS infection:***

- Clinical presentation consistent with STSS or necrotizing fasciitis AND
- Isolation of group A streptococcus by culture or PCR or antigen detection test from a **non-sterile body site** AND
- **No evidence of other pathogen** explaining the clinical presentation

### ***\*Clinical presentation consistent with iGAS:***

Clinically severe illness, **such as** sepsis, septic shock, STSS, pneumonia, meningitis, arthritis, osteomyelitis, myositis or necrotizing fasciitis

### ***Other invasive infection:***

- Clinical presentation consistent with severe disease (e.g. sepsis, meningitis, pneumonia) AND
- Isolation of a pathogen known to cause invasive disease by culture or PCR

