The study will provide in-depth data on the clinical phenotypes, their management and their outcomes, to support clinicians dealing with children with iGAS in their clinical decision making. Increased awareness and early recognition can be lifesaving for children with iGAS and real-time surveillance will help to reduce outbreaks. Furthermore, it will provide public health policy makers with information regarding future NPIs and optimal vaccination schedules regarding other viral infections that may precede iGAS.

iGAS disease is just one example of how the landscape of PID has changed in recent years, and it is currently in a state of ongoing evolution. Other examples include the emergence of novel pathogens and disease entities such as MIS-C and severe hepatitis of unknown origin.

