## **Index visit**

The visit in which the sample is taken that later shows proof of group A streptococcus or another invasive/emergent pathogen.

This is not known at the time of visit, as these results take time.

This does not have to be the first visit in the disease episode.

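### The Part 4 definition of other invasive infection sets no condition on specimen site, so its counts can mix invasive disease with coincident carriage in severely ill children

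*Protocol*

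**What the plan says.** The Definitions section of the protocol sets two conditions for an other invasive infection. The first is clinical: "Clinical presentation consistent with severe disease (e.g. sepsis, meningitis, pneumonia) AND". The second is microbiological: "Isolation of a pathogen known to cause invasive disease by culture or PCR". Neither mentions where the sample came from.

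The iGAS definitions in the same section do. Confirmed iGAS requires "Isolation of group A streptococcus by culture or PCR or antigen detection test from a normally sterile body site". Probable iGAS allows a non-sterile site, but only with "Clinical presentation consistent with STSS or necrotizing fasciitis AND" and "No evidence of other pathogen explaining the clinical presentation".

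The Index visit section defines that visit as "The visit in which the sample is taken that later shows proof of group A streptococcus or another invasive/emergent pathogen". The Introduction explains the wider surveillance in these words: "Other examples include the emergence of novel pathogens and disease entities such as MIS-C and severe hepatitis of unknown origin".

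Under Plan of investigation, Part 4 data are reported monthly and published online monthly. Secondary research question 8 asks whether the network can serve for early alarms.

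**The concern.** An organism that can cause invasive disease can also be carried harmlessly at a non-sterile site. Finding it in the upper airway of a child with pneumonia does not show that it caused the pneumonia. The iGAS definitions guard against this by specimen site or, failing that, by a narrow syndrome and the exclusion of another cause. The definition used for Part 4 has no such guard.

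What is at stake is how a Part 4 count is read. A rise could come from more invasive disease, from more respiratory PCR testing, or from more carriage. If sample site is not recorded, the published series cannot separate these. A second, smaller question is how a syndrome with no identified agent fits an index visit that is defined through a positive sample.

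**Working it through.** The protocol states no figure on this point, so the check is mainly a comparison of its own definitions.

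**Step 1. The definitions side by side**

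| Element | Confirmed iGAS | Probable iGAS | Other invasive infection |
|---|---|---|---|
| Presentation | Severe illness; pneumonia listed | STSS or necrotizing fasciitis only | Severe disease; pneumonia listed |
| Specimen site | Normally sterile | Non-sterile | Not stated |
| Other cause excluded | Not required | Required | Not required |

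Confirmed iGAS does not exclude another cause, but it has the site condition. Probable iGAS relaxes the site condition and in return narrows the syndrome and excludes another cause. Other invasive infection has neither form of protection.

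**Step 2. One case run through the text.** Take a child with severe pneumonia and a positive upper-airway PCR for a non-GAS organism known to cause invasive disease. The presentation condition is met. The microbiological condition is met, because any site will do. The child is counted, whether the organism is the cause or is carried.

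**Step 3. Can it be sorted out later?** The list under Data collection and online database includes culture, PCR and antigen results but names no sample-site variable. The same section tells centres not to keep a local key. If the form does not capture site, it cannot be recovered from the patient's record. The form itself is not shown, so this is a risk and not a certainty.

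**Step 4. Can it be sized?** Not from the documents. Let t be the share of severely ill, tested children whose illness is truly caused by the organism, and c the carriage prevalence at the sampled site. If every true case is detected, the share of counted cases that is coincident carriage is (1 − t)c / [t + (1 − t)c]. With assumed inputs:

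- t = 20%, c = 5%: 0.040 / 0.240 = 17%
- t = 10%, c = 20%: 0.180 / 0.280 = 64%
- t = 5%, c = 40%: 0.380 / 0.430 = 88%

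The answer runs from 17% to 88% on inputs that the protocol does not supply. It shows that the result depends on the assumptions. It is not an estimate for this study.

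**Step 5. Effect on a time series.** If a share s of N severely ill children is tested at a carriage site and true cases are found regardless, the expected count is N[t + (1 − t)cs]. With N, t, c and s constant, carriage raises the level but produces no trend. If s or c rises, the count rises with no change in invasive disease.

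**Step 6. Index visit.** The definition needs a sample that later proves a pathogen. Severe hepatitis of unknown origin has, by its own description, no established cause, so such a case has no defined index visit. Inclusion is a separate matter: it is set by the Inclusion criteria and by the definition of emergent infectious disease, and neither refers to the index visit.

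**The case against.** The best defence is that a broad definition is a legitimate choice. Early alerting across unspecified pathogens favours sensitivity, and a steady background of carriage does not by itself create an increase. Both points stand. They are reasons to keep non-sterile-site cases in surveillance and not to base alarms on confirmed cases only. They are not reasons to leave the two kinds of case indistinguishable.

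Several stronger readings are tempting, and the documents do not support them:

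- **Carriage alone is counted.** It is not. A severe presentation is always required as well.
- **GAS from a throat swab in pneumonia re-enters as an other invasive infection.** The word other, and the Index visit wording that sets group A streptococcus apart from other pathogens, most naturally exclude GAS.
- **Syndromes without an agent are never captured.** The index visit is not an inclusion criterion. The emergent-disease definition covers previously unknown or undetected agents and has a branch on geographic spread, so such cases can arguably be included.
- **Such cases cannot be dated.** The database records the month and year in which the child presented, which is enough for monthly counts.
- **False alarms are shown.** They would need testing or carriage to change over time, and the documents do not speak to that.

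**Conclusion.** The point holds as a gap in one definition. Part 4 counts can include severely ill children whose only positive sample is from a non-sterile site and reflects coincident carriage, and those counts may move with respiratory PCR use. This rests on the wording alone and on its contrast with the iGAS definitions. The size is unknown.

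The effect is confined to secondary research question 8. The three primary questions concern iGAS, whose definitions are specific. Case definitions decide who enters the database, and a later analysis plan could not supply a sample site that was never collected, so the protocol is the place to settle this.

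The index-visit gap is minor: a missing definition for cases without a proven pathogen, and no more than that.

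**What to change.** 1. Split other invasive infection into two tiers that mirror iGAS. Confirmed: a severe presentation with a non-GAS pathogen from a normally sterile site. Probable: a severe syndrome with the pathogen from a non-sterile site and no other pathogen explaining the presentation.
2. Add sample site to the variables under Data collection and online database.
3. Publish the two tiers separately each month and keep both in surveillance.
4. Add a branch to the Index visit definition for cases without a proven pathogen, such as the first visit at which the syndromic case definition is met.

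The cost is a few lines of wording and one form field. The downside is that some true cases diagnosed only from non-sterile samples will be labelled probable. In addition, a non-sterile isolate in a child whose illness another pathogen explains would fall in neither tier for that organism.

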### ***Emergent infectious disease:***

- Infectious diseases by previous unknown or undetected infectious agents that have recently appeared within a population or infectious diseases whose geographic range is rapidly increasing.

## **Index visit**

The visit in which the sample is taken that later shows proof of group A streptococcus or another invasive/emergent pathogen.

This is not known at the time of visit, as these results take time.

This does not have to be the first visit in the disease episode.

## **Exception from informed consent**

Given the following study characteristics, we would request an exception from informed consent.

- Data collection will take place retrospectively for the retrospective study as well as the surveillance study.
- Inclusion can only take place retrospectively, as upon patient presentation, culture results are not available yet.
- Data will be collected completely anonymously
- Data consist of routine care data
- No intervention will take place and collecting data will pose no risk to patients
- Asking parents informed consent whose child suffered from critical illness or has died will pose a considerable burden to them and can lead to response bias
- Data is intended for public health surveillance. The WHO states the following: "Individuals have an obligation to contribute to surveillance when reliable valid, complete data sets are required and relevant protection is in place. Under these circumstances consent is not ethically required." (3)

## **Data collection and online database**

The following variables will be collected: age, time of visit, gender, comorbidity, vaccination status, (viral) co-infection, e.g., VZV, influenza, respiratory syncytial virus (RSV), clinical symptoms, duration of symptoms before treatment, clinical diagnosis (e.g., pleural empyema, necrotising fasciitis, sepsis), culture/PCR/antigen detection results, *emm* type, antimicrobial resistance, treatment, hospital admission, ICU admission and death within 30 days.

During both the retrospective study as well as the surveillance study data will be collected anonymously in an online secure research database, hosted in the EU. Date of birth will be collected

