**Research protocol: PEGASUS: Paediatric European Group A Streptococcal United Study.**

**Version 1.4. 09-07-2024.**

*Retrospective study:*

Participating centres will be asked to report all iGAS cases in the specified time period.

Anonymized data will be collected in an online database. Data will be combined into one dataset and then compared and analysed in combination and per country. Insights from the retrospective data collection phase will be used for the development and implementation of the surveillance part of the study.

*Surveillance study:*

An online database will be used that for all new iGAS cases. Data collection will take place retrospectively once a month. Reporting by the participating centres will take place once a month and reminders will be sent regularly.

The data will be published online on a monthly basis without information that can be traced back to individual patients. Online data will be displayed as numbers as well as visually.

*Setting survey:*

An online survey will be sent to the lead investigators of each participating centre to collect information on national and regional aspects of healthcare possibly impacting iGAS incidence and the care for children with iGAS, such as vaccination schedules and vaccination rates and primary care availability.

*Surveillance study for other invasive or emergent infectious diseases*

An online database will be used for other invasive or emergent infectious diseases. Data collection will take place retrospectively once a month. Reporting by the participating centres will take place once a month and reminders will be sent regularly.

The data will be published online on a monthly basis without information that can be traced back to individual patients. Online data will be displayed as numbers as well as visually.

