**Time period**

- 1) January 2015 to April 2023\*
- 2) April 2023 – onwards

\* For the primary research questions, data collection will take place starting from 2018.

For the secondary research questions, data collection will take place from 2015 for those settings where this data is available and easily retrievable, for all other settings, data collection will take place from 2018.

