## **Research protocol: PEGASUS: Paediatric European Group A Streptococcal United Study.**

**Version 1.4. 09-07-2024.**

as rounded age and time of visit will be collected as shift (day, evening, night), month and year of presentation to ensure patient data cannot be traced back to individual patients. To ensure data will remain truly anonymous, settings will be instructed to not store a local key that can link database data to local patient data.

In case of existing surveillance (UK, Switzerland), existing data will be exported anonymously and combined into a database containing data from all participating countries. Harmonization of data will take place to ensure the comparability and completeness of the collected data.

A survey per hospital will collect information on national and regional aspects of healthcare, such as vaccination schedules, vaccination rates, availability of primary care, funding of health care system, availability of rapid testing for group A streptococcal disease, and COVID NPI's.

After data collection, data will be stored and analyzed on a local secure hospital server of Noordwest Ziekenhuisgroep.

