### **Timetable**

|                                                            |         |
|------------------------------------------------------------|---------|
| Part I: Completion of research protocol                    | 2023 Q1 |
| Part I: Obtaining local medical ethical committee approval | 2023 Q1 |
| Part I: Collecting clinical information                    | 2023 Q2 |

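### Monthly surveillance entry with no minimum delay and no local key can leave 30-day deaths unrecorded, and the record does not show which cases had incomplete follow-up

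*Protocol*

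**What the plan says.** The variable list in the protocol section Data collection and online database ends with "hospital admission, ICU admission and death within 30 days". The 30-day window is attached to death. Its starting point is not given, although the section Index visit defines a visit that could serve.

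For surveillance, the Plan of investigation says "Data collection will take place retrospectively once a month" and "Reporting by the participating centres will take place once a month and reminders will be sent regularly". This fixes how often data are collected, not how long after the visit a case may be entered. No later update of outcome is described.

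On anonymity, Data collection and online database says "settings will be instructed to not store a local key that can link database data to local patient data", and that "time of visit will be collected as shift (day, evening, night), month and year of presentation". The day of the visit is not held.

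Under Time period, the retrospective part covers "January 2015 to April 2023" (from 2018 for the primary questions) and surveillance covers "April 2023 – onwards". The Timetable puts "Part I: Collecting clinical information" in 2023 Q2 and the start-up of the surveillance system in 2023 Q3-4.

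**The concern.** Each rule is reasonable alone; the difficulty lies in the combination. A 30-day outcome needs either entry after day 30 or a way to return to the record. The protocol requires neither, and by forbidding a key it removes the dependable form of the second. A centre with few cases might still recognise its own record from age, month and shift, but a study cannot rely on that.

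The loss could not be repaired at analysis. A child entered on day 10 as alive looks the same as a child alive at day 30. Because the day of visit is not stored, even an automatic entry date, which the protocol does not mention, would leave follow-up uncertain by up to a month.

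Two primary questions are exposed. Question 2 asks whether outcome changed across the periods before, during and after the NPIs. Question 3 compares outcome between countries. Outcome is also a stated aim of the surveillance part. If surveillance records have shorter follow-up than retrospective ones, or if some countries enter cases sooner than others, part of an observed difference in fatality could reflect entry timing.

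**Working it through.** The protocol states no fatality, time to death or entry delay, so there is no figure of its own to reproduce. The check asks how much could be lost over a range of assumptions.

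**Inputs from the protocol:** monthly entry; a 30-day window for death; no later update.

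**Assumptions:** index visits spread evenly over a 30-day month; all cases of a month entered once, L days after it ends; 30 days counted from the index visit; exponential time to death among 30-day deaths (truncated at day 30), with median parameter m days.

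**Follow-up at entry.** A visit made v days before month end has v + L days of follow-up, with v uniform on 0 to 30. Mean follow-up is 15 + L days. For L up to 30, the share with less than 30 days is (30 − L)/30:
- L = 0: mean 15 days; essentially all cases are short of 30 days
- L = 7: mean 22 days; 23/30 = 77% are short
- L = 14: mean 29 days; 16/30 = 53% are short
- L = 30: none are short

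**Share of 30-day deaths missed.** With λ = ln 2/m and S = exp(−30λ), averaging over v gives

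missed = { [exp(−Lλ) − S]/λ − (30 − L)·S } / { 30·(1 − S) }.

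At L = 0 this reduces to 1/(30λ) − S/(1 − S).
- m = 2, L = 0: λ = 0.3466, S = 0.00003; 1/10.397 − 0.00003 = 0.096.
- m = 10, L = 0: λ = 0.0693, S = 0.125; 1/2.079 − 0.125/0.875 = 0.481 − 0.143 = 0.338.
- m = 10, L = 14: exp(−14λ) = 0.379; [(0.379 − 0.125)/0.0693 − 16 × 0.125]/(30 × 0.875) = (3.663 − 2)/26.25 = 0.063.

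| Lag L (days) | m = 1 | m = 2 | m = 5 | m = 10 |
|---|---|---|---|---|
| 0 | 4.8% | 9.6% | 22.5% | 33.8% |
| 7 | 0.0% | 0.8% | 7.7% | 16.0% |
| 14 | 0.0% | 0.1% | 2.3% | 6.3% |
| 30 | 0% | 0% | 0% | 0% |

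A 30.4-day month changes little: at L = 0, 9.5% for m = 2 and 33.4% for m = 10.

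**Effect on a comparison.** With month-end entry and m from 2 to 10, the recorded fatality is the true value times 0.90 to 0.66. An assumed true fatality of 10% would be recorded as 9.0% to 6.6%, against about 10% in data with complete follow-up.

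**Which data are affected.** Retrospective cases run to April 2023 and are entered in 2023 Q2, so nearly all have passed day 30. The Introduction places the NPIs between 2020 and early 2022, so retrospective data from 2018 to April 2023 already span all three periods. Question 2 is therefore affected only if surveillance cases are added to the last period. The protocol neither plans nor excludes this.

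**The case against.** The strongest reply is that the protocol is silent on delay rather than wrong. Collection is described as retrospective, inclusion waits for culture results, and listing a 30-day outcome is compatible with entry after day 30. Entry timing is often left to data-entry instructions. This stands to the extent that loss of deaths is a risk and not a certainty. It does not remove the point, because the ban on a key makes an early entry irreversible in practice, and the protocol is where that ban is set.

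A reader might infer that deaths are missed after April 2023 but not before. The documents do not support so clean a break. The surveillance system is implemented in 2023 Q3-4, so cases from April 2023 until then were probably entered late with full follow-up. Some retrospective cases from April 2023, if entered early in Q2, could be incomplete. UK and Swiss data are exported from existing systems and may not follow the monthly entry at all.

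A reader might also infer that the primary comparison over time is biased. That holds only if surveillance cases are pooled into the period after the NPIs; the retrospective data can answer question 2 alone.

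Finally, a reader might extend the point to ICU admission, *emm* type and resistance results. The text gives no window for ICU admission and no laboratory turnaround time, so neither the size nor the direction of any loss can be derived.

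**Conclusion.** The concern holds as a conditional one. Monthly entry, an outcome window with no starting point, no key and month-level dating together allow 30-day deaths to go unrecorded, without a reliable way to correct or detect it. Any error would lower recorded fatality in the surveillance data.

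The size depends on two quantities that the documents do not give. If deaths come early or entry is even one to two weeks after month end, the loss is small; it becomes material with month-end entry and later deaths. The exponential form is also an assumption: evenly spread deaths would give 50% missed at month-end entry and 14% at a 14-day lag.

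It reaches question 2 only through pooling. It reaches question 3 if entry delay differs between countries, which is possible because some countries export existing data while others enter cases themselves. It deserves a protocol change because it cannot be put right at analysis, but it is not evidence that results are already biased.

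**What to change.** In Data collection and online database, state that death is counted within 30 days of the index visit. In the surveillance paragraph of the Plan of investigation, state that an individual record is entered only after day 30. In the model above this brings both the share of incomplete cases and the share of missed deaths to zero.

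If earlier entry must be kept, add a yes/no field for whether the full 30 days had elapsed at entry. Restrict fatality comparisons, and any outcome shown online, to records marked yes. Records already entered without the field would count as unknown, unless the month of entry shows that 30 days must have passed.

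The cost is a few sentences of protocol and reporting instruction, or one database field. Anonymity is unchanged. Adding a key would be a poorer remedy, because the request to waive consent relies on complete anonymity. The downside of the first option is that individual-level surveillance data appear about one month later. If timeliness matters, an interim case count can feed the dashboard; that is optional and adds some reporting work for centres.
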